### Randomisation and blinding

Patients are randomised in a 1:1 ratio to an individualised pneumoperitoneum pressure strategy (the intervention group) or a standard pneumoperitoneum pressure strategy (the control group). Local investigators perform randomisation using a web-based automated randomisation system (Biostatistics Unit of the Health Research Institute La Fe, Valencia, Spain). Randomisation is performed with random block sizes and is stratified per centre. While attending anaesthesiologists are aware of the assigned pneumoperitoneum pressure strategy, the attending surgeons as well as the patients remain unaware of the assigned pneumoperitoneum pressure strategy at all times, i.e. before surgery, during surgery and after surgery. The PQRS is a patient-reported outcome (PRO), meaning that the investigator has little room to cause bias. The pneumoperitoneum insufflator screen is covered by a surgical drape. Study team members, who are not blinded to randomisation, perform postoperative PQRS measurements.

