### Primary outcome

The primary outcome is the recovery of the PQRS at postoperative day 1 (POD1) (see the subsequent sections for details).

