### Post-operative Quality of Recovery Scale

The PQRS is a validated multidimensional PRO tool [29–31] designed to assess patients’ recovery to baseline status in the postoperative period (www.postopqrs.com). In every patient a baseline measurement of PQRS is performed prior to surgery. After surgery, the measurement of the PQRS is repeated at 15 min (T15) and at 40 min (T40) after arrival in the PACU, as well as in the ward on the morning of POD1 and POD3. The PQRS is a verbal survey tool that depicts recovery in the following five domains: physiologic, nociceptive, emotive, functional, cognitive, and also collects overall patient perspective. Each of these domains is assessed with multiple items on an ordinal scale and compared with baseline to evaluate recovery (see Table 2 for details). Recovery is a dichotomised outcome defined by a return to at least baseline values or better at each of the postoperative measurement time points. Overall recovery requires recovery in all domains being assessed, and failure in any domain results in failure of overall recovery.

**Table 2 Tab2:** Post-operative Quality of Recovery Scale (PQRS)

Domain	Variable	Score	Baseline	T15	T40	POD1	POD3
Physiologic	Blood pressure	1–3	+	+	+	+	+
Physiologic	Heart rate	1–3	+	+	+	+	+
Physiologic	Temperature	1–3	+	+	+	+	+
Physiologic	Respiration	1–3	+	+	+	+	+
Physiologic	SpO2	1–3	+	+	+	+	+
Physiologic	Airway	1–3	+	+	+	+	+
Physiologic	Agitation	1–3	+	+	+	+	+
Physiologic	Consciousness	1–3	+	+	+	+	+
Physiologic	Activity on command	1–3	+	+	+	+	+
Nociceptive	Pain	1–5 Likert	+	+	+	+	+
Nociceptive	PONV	1–5 Likert	+	+	+	+	+
Emotional	Sadness/depression	1–5 Likert	+	+	+	+	+
Emotional	Anxiety/nervousness	1–5 Likert	+	+	+	+	+
Functional	Stand	1–3	+	–	–	+	+
Functional	Walk	1–3	+	–	–	+	+
Functional	Eat/drink	1–3	+	–	–	+	+
Functional	Get dressed	1–3	+	–	–	+	+
Cognitive	Name, city and DOB	TF 0	+	–	–	+	+
Cognitive	Numbers forward	TF 2	+	–	–	+	+
Cognitive	Numbers backwards	TF 1	+	–	–	+	+
Cognitive	Word task: list	TF 3	+	–	–	+	+
Cognitive	Executive memory	TF 3	+	–	–	+	+
Overall patient perspective	Ability to work	1–5	–	–	–	–	+
Overall patient perspective	Ability to perform ADLs	1–5	–	–	–	–	+
Overall patient perspective	Clarity of thought	1–5	–	–	–	–	+
Overall patient perspective	Satisfaction anaesthesia care	1–5	–	–	–	–	+

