### Analysis plan

The statistical analysis plan (SAP) is specified before enrolment of the first patient. In the absence of studies assessing differences in recovery, based on intraoperative IAP management during laparoscopic colorectal surgery, we performed the sample size calculation assuming an odds ratio of 2.65 (equivalent to a difference of 0.5 unit in the logit scale) between groups in the recovery of physiologic PQRS score. It was estimated that a sample size of 170 patients is required to achieve 80% power at a significance level of alpha = 0.05. All reasons for dropouts, expected to be as low as 10%, will be collected and reported. Conversion to open surgery was the main reason for dropouts in the previous study. We will recruit a total of 190 patients to compensate for potential losses.

All analyses will be performed with R software (R Foundation for Statistical Computing, Vienna, Austria). Data will be expressed as the mean (standard deviation, SD) or median (interquartile range, IQR) for continuous variables depending on their distribution (normality will be checked with the Shapiro-Wilks test) and by counts and proportions for categorical variables. The 95% confidence intervals will be calculated for each of the estimated percentiles. The statistical significance level will be set at *P* < 0.05.

The analysis of the primary endpoint follows the intention-to-treat principle. The difference between the recovery PQRS score between groups, the primary outcome on POD1, will be assessed by mixed ordinal logistic regression introducing the patient as random factor, and age, weight, BMI and sex as covariables. The differences in Clavien-Dindo grading of postoperative complications will be assessed by ordinal regression.

For IAV calculation the relationship between IAP and the insufflated volume of CO_2_ will be determined for each patient during initial pneumoperitoneum insufflation. The relationship between IAP and IAV was analysed by linear interpolation from the individual IAP/IAV curves to determine the actual IAV at which surgery is performed. The IAP before CO_2_ gas insufflation was considered the basal IAP or IAP at volume zero, and it was estimated by fitting multiadaptive linear regression splines to the IAV and IAP relationship.

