This study has limitations. We exclude ASA IV patients, who could benefit more from working with low IAP. Since we test a multifaceted strategy, it will remain uncertain which part of the strategy will have the largest impact. In fact, it could very well be that not all parts have the same magnitude of effect, and it is even possible that some parts have negligible  effects. Of note, reversal of neuromuscular blockade with sugammadex instead of neostigmine could improve PQRS recovery at T40 although not at POD1 or POD3. Surgeons, blinded for the actual IAP, will evaluate surgical conditions in a practical dichotomous manner as adequate or not, depending on whether any corrective action is needed. This way of measurement might make comparisons with other studies difficult, such as those using the Leiden-Surgical Rating Scale. The anaesthesiologists collecting the PQRS evaluations are not blinded for the assigned strategy, as they were present during the surgical procedure. However, the risk of bias will be very low, as the PQRS is a ‘patient-reported’ outcome, and the patients remain blinded at all times, including the time at which the PQRS score is collected. We calculated the sample size of our study on PQRS differences; thus, our sample could be underpowered for some secondary outcome that can potentially require a larger sample. In conclusion, the IPPCollapse-II study is designed to test if an individualised pneumoperitoneum pressure and optimised management versus conventional care will affect the outcome of patients undergoing colorectal laparoscopic surgery using relevant patient-centred outcomes.

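### The only stated power (80% with 170 patients) is for recovery of the physiologic PQRS domain; power for the primary outcome, recovery of the PQRS on POD1, is unstated and could lie well below or above 80%

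*Protocol article*

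**What the plan says.** **Sample size.** The Analysis plan section makes the trial's only power statement. It works "assuming an odds ratio of 2.65 (equivalent to a difference of 0.5 unit in the logit scale"), for the difference "between groups in the recovery of physiologic PQRS score", and concludes that "170 patients is required to achieve 80% power at a significance level of alpha = 0.05". It gives no control recovery rate and no time point. Recruitment is raised to 190 for dropout.

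**Primary outcome.** The Primary outcome section reads: "The primary outcome is the recovery of the PQRS at postoperative day 1 (POD1"). The Abstract and the analysis paragraph of the Analysis plan likewise refer to the PQRS without naming a domain.

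**Definition of recovery.** The section on the scale lists five domains: physiologic, nociceptive, emotive, functional and cognitive. It states: "Recovery is a dichotomised outcome defined by a return to at least baseline values or better at each of the postoperative measurement time points". It adds: "Overall recovery requires recovery in all domains being assessed, and failure in any domain results in failure of overall recovery".

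**Planned model.** The Analysis plan compares a recovery PQRS score between arms by mixed ordinal logistic regression with patient as random factor.

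**Discussion.** "We calculated the sample size of our study on PQRS differences", with no domain named.

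**The concern.** The figure that justifies 170 patients concerns one of five domains. All-domain recovery is a different variable. It can be no more frequent than recovery in the worst domain, and its treatment effect depends on what happens in the other four. Nothing in the article names the physiologic domain as primary or argues that it can stand in for the whole scale.

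The risk lies in interpretation. A reader would take 80% as the power of the primary comparison, and the Discussion's general reference to PQRS differences encourages this. A null result on POD1 would then be weighed against a power that was never calculated for it.

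**Working it through.** **Inputs from the article.** Odds ratio 2.65, 80% power, alpha 0.05, 170 patients (Analysis plan); 1:1 allocation (Randomisation and blinding), hence 85 per arm. I assume a two-sided test because sidedness is not stated. All recovery rates below are assumptions because the article gives none.

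**Formulas.** Intervention rate: p₂ = 2.65·p₁ / (1 − p₁ + 2.65·p₁). Power of the pooled two-proportion test, with p̄ = (p₁ + p₂)/2 and n = 85:

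Φ{ [ |p₂ − p₁|·√n − 1.96·√(2p̄(1 − p̄)) ] / √(p₁(1 − p₁) + p₂(1 − p₂)) }

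**Step 1: the plan's own figure.** Without a control rate, 170 cannot be reproduced from stated inputs alone. It comes out if the physiologic control rate is about 0.19 or 0.615. At 0.19, p₂ = 0.383 and p̄ = 0.287, so power = Φ[(1.782 − 1.253)/0.625] = 80%. At 0.615, p₂ = 0.809 and power is again 80%. For dropout, 170/0.9 = 189, so 190 is consistent.

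**Step 2: odds ratio 2.65 applied directly to overall recovery.** Example at a 10% control rate: p₂ = 0.2275, p̄ = 0.164, power = Φ[(1.175 − 1.026)/0.515] = 61%.

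| Control rate | Intervention rate | Power |
|---|---|---|
| 5% | 12.2% | 39% |
| 10% | 22.7% | 61% |
| 20% | 39.8% | 81% |
| 40% | 63.9% | 88% |
| 60% | 79.9% | 81% |

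**Step 3: overall recovery built from the domains.** Assume that the physiologic domain goes from 60% to 80% (odds ratio 2.65), that the other four jointly recover in 25% or 50% of controls, and that the two parts are independent. Overall recovery is the product of the two.

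| Effect on the other four jointly | Other four 25% in controls: overall, power | Other four 50% in controls: overall, power |
|---|---|---|
| None | 15% to 20%, 13% | 30% to 40%, 27% |
| Odds ratio 1.5 | 15% to 27%, 46% | 30% to 48%, 67% |
| Odds ratio 2.0 | 15% to 32%, 75% | 30% to 53%, 87% |
| Odds ratio 2.65 | 15% to 37%, 92% | 30% to 58%, 96% |

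**Step 4: detectable odds ratio** at 80% power for a binary outcome with 85 per arm: 3.24 at a control rate of 10%, 2.61 at 20%, 2.42 at 30%, 2.38 at 40%.

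**Step 5: the effect size itself.** The same sentence equates 2.65 with 0.5 on the logit scale, but ln 2.65 = 0.975 and exp(0.5) = 1.65. At 1.65, power with 85 per arm is at most about 37% at any control rate, whichever binary outcome is used. The calculations in steps 1 to 4 that use 2.65 are conditional on that being the intended value.

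**The case against.** The strongest objection is to inferring that power for the primary outcome is probably far below 80%. A reader might draw that from the all-or-nothing definition, but the article does not support it. The lowest figures require an effect on the physiologic domain and none on the other four. The article never says this: the intervention is multifaceted, and the stated hypothesis concerns recovery of the PQRS as a whole. With a similar effect elsewhere, power exceeds 90%. This objection stands, and the direction of the error is unknown.

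Second, the article never writes that the primary endpoint is overall recovery. That is the natural reading of the Primary outcome section together with the scale's definition, but ordinal regression of a recovery score with a patient random effect does not describe one yes/no result per patient. This also stands. The figures above are scenarios for a binary outcome, not the power of the planned model. It does not rescue the 80%, which would fit only if the physiologic domain were primary, and no section says so.

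Third, the Discussion sentence is imprecise rather than false, since the physiologic score is part of the PQRS. The Discussion also concedes that PQRS differences could be hard to find, which partly tempers the risk of over-reading. Both points are fair.

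**Conclusion.** The mismatch is certain from the text: the 80% power is tied to one domain, while the primary outcome is recovery of the PQRS on POD1. This is not a detail left to a fuller document, because the article states a figure and attaches it to a different variable. Power for the primary outcome is unstated.

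Its size is not determined. The scenarios run from 13% to 96%. They rest on assumed recovery rates, independence between the physiologic domain and the other four, a binary primary variable, a two-sided test, 170 evaluable patients, and 2.65 as the intended odds ratio. A claim that the trial is underpowered goes further than the documents allow. So does a claim that it has 80% power for its primary question.

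**What to change.** 1. Name the primary variable explicitly. Overall recovery on POD1 is the natural reading, but the choice is the sponsor's. Align the planned model with it.
2. State the assumed control rate for that variable.
3. Resolve the conflict between an odds ratio of 2.65 and 0.5 on the logit scale.
4. Replace the 80% sentence with the power, or the minimum detectable odds ratio, for the primary variable at 170 evaluable patients. For a binary outcome the detectable odds ratio is about 3.2 at a 10% control rate, 2.6 at 20% and 2.4 at 30–40%.
5. Label the existing calculation as applying to the physiologic domain only, and make the Discussion sentence say so.

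The cost is wording and a short power table, with no extra patients. The downside is that the stated power may become less favourable.

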Online scale to assess multiple domains of postoperative recovery over time. Timeline: T15–15 min in PACU, T40–40 min in PACU Scoring: Physiologic 1–3; Nociceptive/emotional 1–5, Likert rating scale using a faces pictorial display; Functional: Scored as 3 easily, 2 with difficulty, 1 not at all; Cognitive: Performance variability tolerance factor (TF) is applied. Participants not included in subsequent analysis if baseline scores are equal to or less than the TF *PACU* post-anaesthesia care unit, *POD1* postoperative day 1, *POD3* postoperative day 3, *SpO2* blood oxygen saturation, *PONV* postoperative nausea and vomiting, *DOB* date of birth, *ADL* activity of daily living

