### Data to be collected

Before anaesthesia demographic data will be collected including age (years), gender, body height (centimetres) and body weight (kilograms), BMI (kilograms per metre squared), ASA physical status score, comorbidities, number of previous abdominal surgeries and number of previous laparoscopic surgeries and PQRS score.

During anaesthesia the following data will be obtained: levels of IAPs at which surgery is performed (mmHg) in both groups; proportion of patients who needed a pressure increment to achieve acceptable surgical workspace; IAV at start of pneumoperitoneum (litres); coughing and spontaneous movements (yes/no); type of surgery and oncologic status; duration of surgery (minutes); duration of anaesthesia (minutes); proportion of patients who needed conversion from laparoscopic to open surgery and the reason for it (only if applicable); ventilation data including PEEP, plateau pressure and respiratory driving pressure (ΔP_rs_) (all in centimetres of H_2_O pressure) before pneumoperitoneum generation and during initial IAP titration until a stable level of IAP is reached in both groups; type and dose of neuromuscular blocking agent (milligrams); type and dose of neuromuscular blocking reversal agent (milligrams); total opioid requirement during the first 24 h if used (milligrams); and PDR_ICG_ in the stable pneumoperitoneum phase.

Directly after anaesthesia, in the PACU the following will be obtained: PQRS score at 15 and 40 min after PACU admission and on POD1 and POD3; PQRS score in the morning and peripheral venous blood samples for determination levels of biomarkers.

On all postoperative days until hospital discharge and at day 28 the occurrence of postoperative complications and location will be noted.

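### The primary endpoint is return to the patient's own baseline PQRS, but the stated primary model omits that baseline; the cost is precision, not bias

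*Protocol article*

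**What the plan says.** Three parts of the protocol article bear on this.

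- **Post-operative Quality of Recovery Scale.** The endpoint is binary and referenced to the patient: "Recovery is a dichotomised outcome defined by a return to at least baseline values or better at each of the postoperative measurement time points". For overall recovery, "failure in any domain results in failure of overall recovery". The reference value is always available: "In every patient a baseline measurement of PQRS is performed prior to surgery". The notes to Table 2 add an allowance for one domain: "Cognitive: Performance variability tolerance factor (TF) is applied".
- **Data to be collected.** The items recorded before anaesthesia end with "number of previous abdominal surgeries and number of previous laparoscopic surgeries and PQRS score".
- **Analysis plan.** The primary day 1 comparison uses "mixed ordinal logistic regression introducing the patient as random factor, and age, weight, BMI and sex as covariables". Baseline PQRS is not in that list.

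Because the article names its covariables, this is a stated analysis choice and not a detail left to the statistical analysis plan.

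**The concern.** The baseline score is one side of the inequality that defines recovery. On a 1 to 5 item, a patient who enters at the worst level cannot score lower and so cannot fail that item. A patient who enters at the best level fails it on a one-step drop. Baseline PQRS is therefore linked to the endpoint by construction. Age, weight, BMI and sex have no such built-in link.

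Leaving it out has two costs. Outcome variation that the baseline could explain stays in the error, which lowers power. If the arms differ by chance at baseline, that difference is carried in the estimate and not removed. The patient random factor does not repair this, because a random intercept does not adjust the arm comparison for a baseline difference.

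**Working it through.** **Inputs from the article (Analysis plan):** odds ratio 2.65, alpha 0.05 (taken as two-sided), 80% power, 170 patients, 10% dropout, 190 recruited. **Not given:** control recovery rate, baseline-to-day-1 correlation, item variability. These are assumed below.

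**1. The plan's own figure.** With control rate p, the treated rate is 2.65p / (1 − p + 2.65p). The two-proportion formula gives a total of 166 at p = 20% or 60%, 168 at 25% with continuity correction, and 136 at 40%. So 170 fits an odds ratio of 2.65 for some control rates but cannot be reproduced uniquely. Dropout: 170 / 0.9 = 189, consistent with 190. (The article also equates 2.65 with 0.5 on the logit scale, although ln 2.65 = 0.975. That is a separate matter; 2.65 is used here.)

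**2. Size of chance imbalance.** With 85 per arm, the standard error of the arm difference in a standardised baseline is √(2/85) = 0.153 SD. Assume the baseline carries 0.5 to 1.3 log-odds per SD.

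- One standard error of imbalance shifts the log odds ratio by about 0.5 × 0.153 = 0.08 to 1.3 × 0.153 = 0.20.
- Two standard errors shift it by 0.15 to 0.40.
- The planned effect is 0.975.

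The unadjusted standard error already allows for this variation. Adjustment removes it.

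**3. Power with a single latent score.** Let baseline B = T + e0 and day 1 score Y = T − shift + effect + e1, where T has variance ρ and each error has variance 1 − ρ. A patient is recovered if Y ≥ B. Then the correlation of B with the change Y − B within an arm is −√((1 − ρ)/2), so baseline predicts recovery less as ρ rises. Assumptions: control recovery 40%, treated 1.06/1.66 = 63.9%, N = 170, logistic regression, 1,500 trials per setting.

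| ρ | correlation of B with change | power without | power with | gain (points) |
|---|---|---|---|---|
| 0.3 | −0.59 | 89.4% | 95.3% | 5.9 |
| 0.5 | −0.50 | 88.9% | 93.1% | 4.2 |
| 0.7 | −0.39 | 88.7% | 91.1% | 2.4 |
| 0.9 | −0.22 | 89.5% | 89.6% | 0.1 |

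The closed-form power at 40% with 85 per arm is 88.2%, in line with the third column. The Monte Carlo standard error of each power is about √(0.9 × 0.1/1,500) = 0.8 points. Under no treatment effect, rejection was 3.8% to 5.6% without baseline and 4.5% to 5.3% with it.

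**4. Power with a generic prognostic covariate** (N = 170, 1,500 trials), without and with it in the model: 86.8% and 88.5% at 0.5 log-odds per SD; 87.9% and 89.9% at 0.7; 84.4% and 90.0% at 1.0; 85.5% and 92.5% at 1.3. Gains are 1.7 to 7.0 points.

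**5. Power when every item must recover**, which is closer to overall recovery, with a baseline total as covariate and N = 170:

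- Eight items, most patients near the best score, 400 trials: 76.25% and 76.5%.
- Four or eight items, baseline centred at 4.0 to 5.0 of 5, reading-to-reading SD 0.3 or 0.5, ten settings of 1,500 trials: change of −1.6 to +0.6 points. Rejection under no effect was 5.3% and 5.6%.
- Varying the baseline-to-day-1 correlation: about +2 to +7 points at 0.3, −1 to +3 at 0.5, and −2 to +1 at 0.7 or above.

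All these runs use ordinary logistic regression, not the mixed ordinal model that the article names.

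**The case against.** The strongest reply is that dependence on baseline is what the scale is meant to capture. Each patient is already compared with their own starting point, and one who starts at the best level and drops a step has indeed not returned to baseline. The test is valid without adjustment, the gain is close to zero in several composite models, and nothing in the article supports the upper end of the range. The simulated model is also simpler than the planned one.

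Much of this stands. There is no contradiction in the article and no bias, and the gain under the exact planned model is not shown. But using baseline to define the outcome does not remove its influence on the chance of meeting that outcome, and the near-zero gain holds only in some settings.

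Three stronger readings are tempting and are not supported.

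- A reader might infer that the primary comparison is biased. Randomisation and the error rates above say otherwise.
- A reader might infer that recovery has no tolerance or confirmation anywhere. Table 2 and its notes give the cognitive items tolerance factors of 0 to 3. A recovery state defined on one morning does not evidently need a confirmatory reading.
- A reader might count patients who worsen on one item yet pass it as a cost of the model. Overall recovery needs every assessed domain, and adding a covariate reclassifies nobody.

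The overlap of weight with BMI is likewise no fault in the treatment estimate.

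**Conclusion.** The point holds in a limited form. The stated covariables leave out the one baseline measurement that is tied to the primary endpoint by definition and is already collected in every patient. The consequence is lost precision and less protection against chance imbalance; the type I error is not affected.

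Under the assumed inputs, the power gain from adding baseline PQRS at N = 170 is about 0 to 7 points. The upper part needs a weak baseline-to-day-1 correlation (around 0.3) or a strongly prognostic baseline. The gain is near zero at high correlation or when most patients start near the best score. The worst simulated loss from adding the term is about 1 to 2 points, within simulation error. The article offers no figure that would narrow this range.

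**What to change.** In the Analysis plan, add baseline PQRS as one prespecified fixed covariate in the primary POD1 model: a single baseline total over the domains assessed. State how the total is scored, since the item ranges differ between domains. Use the same term for PQRS recovery at T15, T40 and POD3. At T15 and T40 the functional and cognitive domains are not measured (Table 2), so the total there covers the other three. Make the change by a dated amendment before unblinded outcome data are examined, because the article reports that recruitment has begun.

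The cost is one more model term, with no new data and no change to the conduct of the trial. There is no gain if baseline proves weakly predictive. The odds ratio also becomes conditional on baseline: in the single-score simulation the mean log odds ratio moved from 1.003 to 1.314 at ρ = 0.3 and from 0.983 to 1.023 at ρ = 0.9. The report should therefore say which odds ratio is given. Dropping weight is optional.

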### Substudies

The IPPCollapse-II study has three substudies (see the detailed description in Additional file 4):Levels of biomarkers (neutrophil-lymphocyte ratio, C-reactive protein, interleukin-6 and procalcitonin) are measured in peripheral venous blood samples obtained before surgery and at POD1 and POD3 and compared between the two study groups. For this substudy, blood samples are obtained in all participating centres.Untargeted metabolomic analysis is performed on peripheral venous blood samples and peritoneal tissue, both obtained after initial insufflation of pneumoperitoneum and at the end of the procedure. This substudy includes the first 10 patients in the Hospital Universitari i Politècnic La Fe, Valencia, Spain.Plasma disappearance rate of indocyanine green (PDR_ICG_) after intravenous ICG injection is measured to evaluate hepatic perfusion during pneumoperitoneum as a marker of liver function [28]. This substudy runs only at the University Hospital Gregorio Marañon, Madrid, Spain.

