Differences in continuous variables between groups (IAP, IAV, LOS, inflammatory biomarkers) will be assessed by linear regression or with the Mann-Whitney *U* test (if the normal distribution assumption is rejected by the Shapiro-Wilks test). Differences in ΔP_rs_ between groups will be assessed by linear regression. A multivariable model introducing BMI, previous laparoscopic surgery and age will be fitted for predictive purposes.

Differences in the plasma disappearance rate of ICG are assessed by beta regression. Occurrences of cough or spontaneous movements during anaesthesia are assessed by logistic regression.

The relationship between IAP and IAV will analysed by linear interpolation from the individual IAP/IAV curves. The IAP before CO_2_ gas insufflation (IAP at volume zero) will be estimated by fitting multiadaptive linear regression splines to the IAV and IAP relationship. If a variable has a frequency of missing data > 5%, data will be imputed by the multiple imputation method.

As there is no ethically unacceptable risk related to the primary outcome analysed, there will be no planned interim analysis.

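### The Shapiro-Wilk rule sends skewed biomarkers to a Mann-Whitney test that cannot use the pre-surgery value already drawn; the comparison stays valid but loses precision

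*Protocol article*

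**What the plan says.** The Substudies section of the protocol article lists four markers (neutrophil-lymphocyte ratio, C-reactive protein, interleukin-6 and procalcitonin), measured in all centres in "peripheral venous blood samples obtained before surgery and at POD1 and POD3 and compared between the two study groups".

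The Analysis plan section gives the method: "Differences in continuous variables between groups (IAP, IAV, LOS, inflammatory biomarkers) will be assessed by linear regression". The alternative is the Mann-Whitney U test, used "if the normal distribution assumption is rejected by the Shapiro-Wilks test". No pre-surgery value, change score or repeated-measures term is named for the biomarkers. For the primary outcome the same section does list covariates, "introducing the patient as random factor, and age, weight, BMI and sex as covariables".

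The Randomisation and blinding section says allocation is 1:1 and stratified by centre. The Discussion concedes that differences in PQRS may be hard to find and presents the three substudies as a way to pick up smaller differences, mainly in laboratory values.

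**The concern.** A preoperative value of the same marker is usually the first candidate covariate for its postoperative value. Here it is drawn in every patient, but the rule for comparing groups does not use it.

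The switch makes this worse than an unlisted covariate. Inflammatory markers tend to be right-skewed, and at this sample size Shapiro-Wilk has high power against skewness. The plan is then committed to a rank test, which takes neither baseline nor centre and yields a p-value rather than an adjusted effect with an interval. For a marker with milder skew, the branch taken depends on the sample, so one marker could be analysed by regression on day 1 and by ranks on day 3.

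What is at stake is the ability of the biomarker substudy to show the small differences for which the Discussion says it was set up.

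**Working it through.** **Plan's own figure.** The article gives no effect size, standard deviation, baseline correlation or power for any biomarker, so there is nothing to reproduce on this point.

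**Inputs from the article**
- Patients analysed: 170 ("a sample size of 170 patients is required to achieve 80% power at a significance level of alpha = 0.05"). At 1:1 this is n = 85 per arm, assuming that all analysed patients give samples.
- Significance level 0.05, taken as two-sided because sidedness is not stated.

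**Inputs assumed**
- Lognormal marker.
- Shift between arms δ = 0.4 SD on the log scale.
- Correlation ρ between log baseline and log follow-up of 0.1, 0.3, 0.5 or 0.7.

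**Step 1: where the switch leads.** Shapiro-Wilk was applied to simulated samples of 170 lognormal values:

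| SD of the log values | Share of samples rejected |
|---|---|
| 0.1 | 26% |
| 0.2 | 78% |
| 0.3 | 98.5% |
| 0.5 or more | about 100% |

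From a log-SD of about 0.3 upwards, the rule is in effect a fixed Mann-Whitney test. Only for mild skew does the branch vary from sample to sample.

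**Step 2: power by formula.** The standardised effect without adjustment is δ√(n/2) = 0.4 × √42.5 = 2.608.
- Unadjusted t-test on log values: Φ(2.608 − 1.96) = 74%.
- Mann-Whitney, relative efficiency 3/π on the normal scale: 2.608 × √(3/π) = 2.548, so Φ(2.548 − 1.96) = 72%.
- Log-scale ANCOVA: residual variance is multiplied by 1 − ρ², so power = Φ(2.608/√(1 − ρ²) − 1.96).

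| ρ | 1 − ρ² | 2.608/√(1 − ρ²) | ANCOVA power | Gain over Mann-Whitney (72%) | 170 × (1 − ρ²) |
|---|---|---|---|---|---|
| 0.1 | 0.99 | 2.621 | 75% | 2 points | 168 |
| 0.3 | 0.91 | 2.734 | 78% | 6 points | 155 |
| 0.5 | 0.75 | 3.011 | 85% | 13 points | 128 |
| 0.7 | 0.51 | 3.651 | 95% | 23 points | 87 |

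Gains are taken from unrounded powers. The last column is the number of patients that would give ANCOVA the same precision as an unadjusted log-scale comparison in 170.

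**Step 3: power by simulation.** I ran 10,000 trials per correlation, with 85 per arm and log-SD 0.8. Shapiro-Wilk rejected in every trial. Mann-Whitney power was 71% to 73%. ANCOVA power was 74%, 77%, 85% and 95% for ρ = 0.1, 0.3, 0.5 and 0.7. The gaps are about 2, 6, 12 and 23 points. Shorter runs put the gap at ρ = 0.3 as high as 7 points, which is simulation noise.

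**Step 4: validity.** With no true difference, both methods rejected in roughly 4% to 6% of 4,000 simulated trials per correlation. The stated rule does not inflate type I error.

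**The case against.** **The full documents may already adjust for baseline.** The article is condensed. It says that an analysis plan was fixed before the first enrolment and refers to Additional file 4 for the substudies, and neither is shown. The regression branch names no covariates, but it does not say that the comparison is unadjusted. This stands: a reader might infer that the plan excludes the baseline, and the article does not support that. It does not rescue the switch, which is stated outright and whose second branch cannot hold a covariate.

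**If the pre-test nearly always rejects, little is chosen from the data.** This is fair for strongly skewed markers. Mann-Whitney is then a valid, prespecified test that a log transformation would not change. The criticism there is inefficiency and the lack of an adjusted estimate. Data-driven choice matters only for mild skew.

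**The size rests on assumptions.** This also stands. Mann-Whitney itself costs only about 2 points against an unadjusted log-scale t-test (72% against 74%). The rest comes from the baseline correlation, which the article does not give and which may be low between a preoperative value and one taken after the surgical insult.

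**Driving pressure.** A reader might extend the point to respiratory driving pressure, which is also recorded "before pneumoperitoneum generation and during initial IAP titration until a stable level of IAP is reached in both groups". The documents do not support this. The normality switch does not cover driving pressure: differences "between groups will be assessed by linear regression. A multivariable model introducing BMI, previous laparoscopic surgery and age will be fitted for predictive purposes", so its missing baseline is only an omission. More importantly, the section on the individualised strategy places modified positioning and deep neuromuscular blockade ahead of insufflation. The pre-pneumoperitoneum reading may therefore already reflect allocation, and adjusting for it could remove part of the effect under study. The biomarker baseline is drawn before surgery and does not have this problem.

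**Conclusion.** The point holds for the four inflammatory biomarkers and for nothing else. For markers with a log-SD of about 0.3 or more, the stated rule leads almost surely to a test that cannot use the pre-surgery value or centre and that gives no adjusted effect with a confidence interval.

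The loss of power is small, about 2 to 7 points, if the baseline correlation is 0.1 to 0.3. It is material, about 12 to 23 points, if the correlation is 0.5 to 0.7. These figures assume 85 per arm, a lognormal marker and a 0.4 SD log-scale shift.

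It would be wrong to conclude that the biomarker comparisons are biased or invalid. Randomisation protects the unadjusted comparison, and type I error stays near 5%. The primary outcome is not touched. The Discussion already warns that some secondary outcomes may be underpowered, which is a reason not to give up precision that the collected data can supply. This is an improvement that should be made, not a flaw that threatens the trial.

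**What to change.** For the biomarkers only:
- Remove the Shapiro-Wilk switch.
- Prespecify ANCOVA on log-transformed values at days 1 and 3, or one repeated-measures model over both days, with the log pre-surgery value and centre as covariates.
- Report the ratio of geometric means between arms with its 95% confidence interval at each day.
- State how values below an assay's detection limit will be handled before taking logs.
- Keep Mann-Whitney, if wanted, as a sensitivity analysis.

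Leave the driving-pressure analysis out of this change.

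The cost is wording in the analysis plan, unless the full plan or Additional file 4 already contains it. No extra samples, visits or patients are needed. Because the plan was fixed before enrolment, the change should be dated and made before biomarker results are compared by arm.
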